#### Process items (collected at time 2 and time 3)

This relates to the extent to which educators and practice coaches use the support system and how it affects their views about their work. These items ask how often they are using the weekly strategies that were the focus of the intervention. Practice coaches are asked to reflect on whether the training prepared them adequately for the role. Items for the process questionnaire are designed to measure educator’s confidence and intention to create a positive relational environment using the *Making moments matter* component of the service support system.

### Parent measures

#### Demographics (collected at time 1)

Demographic information includes parent gender and date of birth and whether English is the main language spoken at home. We ask how many children they have at the service, their gender, date of birth and how many days they attend the service each week. Parents also report how long their children have attended the service, whether their children currently attend any other services, and whether they have attended another service previously.

#### Parent questionnaire (collected at time 1, time 2, and time 3)

At each time point we will ask parents about their relationship with educators, how welcome they feel at the service, how satisfied they are with the way educators communicate with them, and whether they have sought help from support services as a result of engaging with their child’s service. Items were devised by the project team and some were adapted from the Parenting Today in Victoria survey [21] conducted by the PRC, the Me as a Parent Scale [22], and the ECEC Exploratory Study.

If a parent has more than one child at the service, we ask them to select the child whose birthday is closest to the date on which they are filling out the questionnaire and respond to items with that particular child and that child’s educator as a reference point. In the case of twins or multiples, we ask parents to think of the eldest. Parents will be asked whether they have raised a concern with an educator and/or an educator has raised a concern with them, and how many times this occurred within the past 4 weeks. If this occurred, they will also be asked how satisfied they were with the interaction.

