### Data collection timepoints

The following measures will be collected online via a secure data system at three time points: Time 1 = 0 weeks (before randomisation to trial conditions), Time 2 = at the end of week 10 (immediately after the intervention group has completed the intervention), and Time 3 = 3 months after the intervention group has completed the intervention and immediately after the control group has completed the intervention. Each questionnaire takes about 10–15 min to complete. To thank participants for their time, after completing the third questionnaire they will be able to download a tailored package of resources about early childhood and development produced by the PRC.

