### Analysis of primary and secondary outcome measures

An intention-to-treat multi-level analysis will be conducted for each of the outcome measures with level 1 data reflecting each assessment period, level 2 data reflecting individual participants and level 3 data reflecting the various services. Changes in the outcome measures will be compared for the intervention and control groups assuming appropriate distributions for the outcome measures. Random intercepts will be assumed, while allowing for the clustered nature of the data, and adjusting for appropriate covariates as fixed effects. The model will include an indicator variable for the study groups (0 = control, 1 = intervention) as a fixed effect at level 3 and an integer time variable (1 = baseline, 2 = time2 and 3 = time3) as a random effect at level 1.

We will report the estimated intervention effect as mean outcome difference for continuous outcomes and odds ratio for binary outcomes between intervention and control groups with 95% confidence intervals and *p*-values [25]. The effect of individual moderators will be incorporated using interaction terms between time, allocated group and the individual moderators [26].

Finally, a completer analysis will be conducted with a repeated measures MANOVA analysis using inverse probability weights to adjust for any attrition bias [27]. This analysis will also account for the correlation between measures from the same participant, while allowing for the clustered trial design.

Furthermore, we will examine responses of the control group before and after receiving the intervention.

As an indication of family-centredness, we will look at items that both educators and parents completed, to compare their perceptions (e.g. whether they both agree the service is a welcoming environment for parents).

All qualitative data (open text questions) will be summarised and examined for themes. Thematic analysis is a multi-stage process involving familiarisation with the data, coding (identifying important features relevant to the research questions), searching for and reviewing themes, and defining and naming them [28].

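### The index child is tied to the completion date of a three-wave questionnaire, so parents with several children may rate a different child at Times 2 and 3, adding noise to within-parent change

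*Protocol article*

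**What the plan says.** The rule stands in the protocol article under the heading "Parent questionnaire (collected at time 1, time 2, and time 3"). A parent with several children at the service is told how to pick one: "we ask them to select the child whose birthday is closest to the date on which they are filling out the questionnaire". The parent must then "respond to items with that particular child and that child’s educator as a reference point". Twins and multiples have their own rule: "In the case of twins or multiples, we ask parents to think of the eldest".

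The same section makes clear that the items recur: "At each time point we will ask parents about their relationship with educators". Under Trial outcomes, a parent primary outcome is satisfaction with the dealings parents have with their child's educator. The stated expectation there is a larger change from Time 1 to Time 2 in the intervention group, held or improved at Time 3. The analysis section says "Changes in the outcome measures will be compared for the intervention and control groups".

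Under Consent and recruitment, the three questionnaires are linked by a participant code. Under Modelling strategy and the outcome analysis, the repeated unit is the individual participant, nested in the service. No section mentions a child code or says that the child chosen at Time 1 is used again.

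**The concern.** A closest-birthday rule is a sound way to pick one child at random in a single survey. In a repeated survey it has a side effect: the anchor is the day of completion, so the chosen child can change as the year moves on. Only the rule for twins gives the same child at every wave.

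When the child changes, the educator being rated may change too. That parent's difference between waves then mixes real change with the difference between two children and perhaps two educators. At stake is the precision of the parent primary outcome and of other items about a particular child or educator, such as satisfaction with discussing concerns.

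**Working it through.** The article gives no figure on this point, so there is none to reproduce. The check asks how often the rule changes the child, and what that does to the variance of change.

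**Inputs from the protocol article**
- Time 1 is at week 0 ("Time 1 = 0 weeks (before randomisation to trial conditions"), Time 2 at the end of week 10, and Time 3 three months after that (Data collection timepoints). Taken as days 0, 70 and 161.
- 302 parents completed Time 1 (Participants).

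**Assumptions, not in the article**
- Two non-twin siblings, both still enrolled, with independent birthdays spread evenly over the year.
- 10–30% of parents have more than one child at the service.
- Ratings by one parent at two waves correlate 0.6 for the same referent and 0.3 for a different one, taking a different child to mean a different educator. Variance is 1 at each wave.

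**Step 1: chance of a switch, closest birthday in either direction.** For two birthdays, the dates equally far from both lie exactly half a year apart. For a gap g under 182.5 days, at most one such date is crossed, so P(switch) = 2g/365.
- Time 1 to Time 2: 2 × 70/365 = 0.38
- Time 1 to Time 3: 2 × 161/365 = 0.88

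Hence about 12% keep the same child at all three waves. A simulation of 400,000 families gave 0.384 and 0.881. Moving the waves to days 63/154 or 84/175 gives 34–46% at Time 2 and 84–96% at Time 3. With three children, the simulation gave 55% and 98%.

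**Step 2: the next-birthday reading.** The child changes if exactly one of the two birthdays falls in the gap: P(switch) = 2s(1 − s), with s = g/365.
- Time 2: 2 × 0.192 × 0.808 = 0.31
- Time 3: 2 × 0.441 × 0.559 = 0.49

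**Step 3: share of all parents who switch (closest-birthday reading).**

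| Multi-child share (assumed) | By Time 2 | By Time 3 |
|---|---|---|
| 10% | 0.10 × 0.384 = 3.8% (about 12 of 302) | 0.10 × 0.882 = 8.8% (about 27) |
| 30% | 0.30 × 0.384 = 11.5% (about 35) | 0.30 × 0.882 = 26.5% (about 80) |

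These counts are before attrition and treat every multi-child parent as having two children.

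**Step 4: variance of individual change.** Var(change) = 2(1 − r).
- Same referent: 2(1 − 0.6) = 0.8
- Different referent: 2(1 − 0.3) = 1.4, which is 75% more, in switchers only

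Over all parents, the relative rise is the share switching × 0.75, and the standard error grows by the square root.

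| Multi-child share | Variance rise, Time 2 | SE rise | Variance rise, Time 3 | SE rise |
|---|---|---|---|---|
| 10% | 2.9% | 1.4% | 6.6% | 3.2% |
| 30% | 8.6% | 4.2% | 19.8% | 9.5% |

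The standard-error figures cover the individual-level part alone. Variance between services is not changed by switching, so the loss in the full cluster analysis is smaller.

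**The case against.** Four objections carry weight.

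- **Re-application is inferred.** The article does not say that parents choose afresh at each wave, and the form may already name the child at Times 2 and 3. The heading and the wording make re-application the natural reading, but not a certain one. This stands, and the point is conditional on it.
- **No bias between arms.** A reader might infer that the treatment comparison is distorted. The article does not support that. Birthdays are independent of allocation, and the intervention is service-wide: all educators were required to implement it. A sibling's educator therefore works under the same allocation.
- **No parent–educator pair is modelled.** A reader might infer that the analysis assumes one fixed pair per record. It does not: its levels are assessment, participant and service. The results it reports are group differences, not individual change.
- **The 75% figure is not a trial-wide figure.** It describes switchers only, under assumed correlations. Siblings may also share an educator, which would shrink it.

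The scope is limited as well. Parenting confidence and stress belong to the parent, and inclusiveness and supportiveness belong to the service; both depend little on the index child. The educator primary outcome is untouched.

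What remains is that the written rule does not hold the rated child constant in a design built on change over time, and that this costs precision for no gain.

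**Conclusion.** The point holds as a matter of precision. On the plain reading, a change of child is common among parents with two non-twin children at the service: about 38% at Time 2 and 88% at Time 3, or 31% and 49% on the next-birthday reading. The trial-wide effect is modest, at about 3–9% more individual-level change variance at Time 2 and 7–20% at Time 3. That is roughly 1.5–4% and 3–10% in standard error, and less once between-service variance is counted.

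The switching probabilities rest on uniform, independent birthdays and the planned wave dates. The trial-wide figures also rest on the assumed multi-child share and correlations, none of which the article states. The point does not threaten the validity of the comparison between arms.

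**What to change.** State that the index child is the one chosen at Time 1, and name or prompt for that child in the Time 3 questionnaire, unless the form already does so. Trial status says follow-up data were still to be collected, so this was open at the time of writing.

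For Times 1 and 2, derive the likely index child from completion dates and the children's dates of birth; the Time 1 demographics record them ("We ask how many children they have at the service, their gender, date of birth"). Flag parents whose child probably changed, and add a sensitivity analysis of the parent outcomes restricted to same-child records.

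The cost is a prompt in the online form, linked through the participant code, and one derived variable. There are two drawbacks. Time 2 may stay on the completion-date rule, so a two-child parent would still differ in referent between Times 2 and 3 with probability about 38%, against 2 × 91/365 = 50% if nothing changes. The same-child analysis also uses somewhat fewer parents: on the assumptions above, it drops about 12–35 of 302 at Time 2. The derived child is what the rule implies, not necessarily the one the parent had in mind.

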### Trial outcomes

The primary outcomes of the trial are educator confidence and skills in working with parents, and parent satisfaction with interactions with their child’s educator. Secondary outcomes include parent inclusiveness at centre, supportiveness of centre, parenting involvement with their child’s centre and learning, staff satisfaction with using *Partnering with Parents*, parent satisfaction with discussing concerns with educators, and parent psychological distress (parenting competence and confidence, parenting stress). We expect there will be greater change from Time 1 to Time 2 for the intervention group than for the control group and we expect that the change will be maintained or further improved at three-month follow-up (Time 3).

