### Baseline analysis (time 1)

As a check for appropriate balance between the control and intervention groups and to provide an overview of the study population [24], both at service and individual levels, data for the control and intervention groups will be compared at baseline. We will present the mean, standard deviation and range for continuous, approximately symmetric variables; medians, interquartile range and range for continuous, skewed variables of clusters. We will describe categorical data with percentages across sub-groups.

All statistical tests and confidence intervals will be two-sided. Between-group comparisons will be presented with 95% confidence intervals and the statistical significance level set will be at the 5% level. In addition, we will account for the clustered nature of the data for all comparative analyses to ensure correct confidence intervals and type I error rates are calculated. In addition, the intra-cluster correlation coefficient for each outcome, based on the adjusted analyses with 95% confidence interval, will be reported.

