### Power analysis

The number of parents recruited for this study is 302. However, the effective sample size is less than this because we have intra cluster correlation (ICC), the value of which is unknown. The required effective sample size to detect a moderate effect size (d = 0.5) with 5% significance and 80% power is 102, which suggests that the sample size recruited is adequate as long as attrition rates are less than 50%, when the ICC is 3% (or less than 33% when the ICC is 6%).

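### The Time 3 arm difference cannot show whether the gain is maintained, because control services have also had the programme; assess maintenance within the intervention arm as an uncontrolled estimate

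*Protocol article*

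**What the plan says.** Under Trial outcomes the protocol article states two expectations. The first is a comparison of arms: "We expect there will be greater change from Time 1 to Time 2 for the intervention group than for the control group". The second concerns durability: "we expect that the change will be maintained or further improved at three-month follow-up (Time 3".

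Data collection timepoints defines Time 3 as "3 months after the intervention group has completed the intervention and immediately after the control group has completed the intervention".

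Analysis of primary and secondary outcome measures sets out a three-level model over all three assessments, with a group indicator (0 = control, 1 = intervention) and an integer time variable. The intervention effect is to be reported as a difference between the groups (an odds ratio for binary outcomes), with 95% confidence intervals and p-values. The same section adds that the control group's responses before and after receiving the programme will be examined. It names no corresponding analysis for the intervention group.

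The general rule on inference stands under Baseline analysis: "All statistical tests and confidence intervals will be two-sided", and "the statistical significance level set will be at the 5% level".

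**The concern.** The second expectation is about what happens to the intervention group's gain after the programme ends. The effect measure that the article describes is a contrast with the control group. At Time 2 that contrast sets treated services against untreated ones and answers the first expectation. At Time 3 it sets services three months past the programme against services that have just finished it. It then mixes two things: how much of the intervention arm's gain remains, and how much the controls have gained.

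Durability is half of the stated expectation. A shrinking arm difference at Time 3 could be taken for a fading effect when the controls have simply caught up. A difference that persists could be taken for durability when the programme merely did less in the control services. Neither reading would be sound.

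**Working it through.** **1. Is there a figure in the plan to reproduce?** None for Time 3. The only planning figure is in Power analysis: "The required effective sample size to detect a moderate effect size (d = 0.5) with 5% significance and 80% power is 102". It concerns detecting a difference and says nothing about maintenance. It reproduces as a one-sided 5% t-test with 51 per arm, while a two-sided test needs 126 to 128. That is a separate matter and does not affect this point. Below, 0.5 SD is used only as a scale.

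**2. What the Time 3 arm difference measures.** Let g be the intervention arm's programme gain at Time 2, L the part lost by Time 3, and h the control arm's programme gain at Time 3. Any time trend common to both arms cancels.

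- Time 2 arm difference = g
- Time 3 arm difference = (g − L) − h

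With g = 0.5 SD:

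| Situation | L | h | Time 3 difference |
|---|---|---|---|
| Gain fully kept, controls match it | 0 | 0.50 | 0.50 − 0 − 0.50 = 0 |
| Half lost, controls gain half | 0.25 | 0.25 | 0.50 − 0.25 − 0.25 = 0 |
| Gain fully lost, controls gain nothing | 0.50 | 0 | 0.50 − 0.50 − 0 = 0 |

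Full maintenance and complete loss can give the same result. L and h cannot be separated from the arm difference.

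**3. Does pooling the three times help?** No. If the group effect were read from a straight-line slope on time coded 1, 2, 3 with complete data, each arm's slope is (Time 3 − Time 1)/2 and Time 2 drops out. In the first row of the table both slopes are 0.50/2 = 0.25, so the slope difference is 0 although the Time 2 effect is 0.5 SD. If instead the arm difference were averaged over the three times, it would be (0 + 0.50 + 0)/3 = 0.17. The article does not say which coefficient is the effect. Either way, Time 3 data from treated controls should not enter the randomised estimate.

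**4. How precise is the within-arm alternative?** The article does not give the inputs for this, so the following is an illustration. Assumptions:

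- Half of each sample is in the intervention arm: 118/2 = 59 educators and 302/2 = 151 parents.
- There are J = 19/2 = 9.5 services in the arm.
- The Time 2 to Time 3 correlation r is 0.5 to 0.7.
- The service-level variance of change s² is 0 to 0.03 SD².
- Attrition is 0%, 33% or 50%. The last two are the limits in Power analysis, which were stated for parents only.
- The t critical value on J − 1 = 8.5 df is 2.28.

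Standard error of the change = √(2(1 − r)/n + s²/J). The 95% half-width is 2.28 × SE.

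Example, educators with 33% attrition, r = 0.5, s² = 0: n = 59 × 0.67 = 39.5; SE = √(1/39.5) = 0.159; half-width = 2.28 × 0.159 = 0.36 SD.

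Over the assumed ranges the half-width is:

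- educators: 0.23 to 0.32 SD with no attrition, 0.33 to 0.44 SD at 50%;
- parents: 0.14 to 0.23 SD with no attrition, 0.20 to 0.29 SD at 50%.

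**5. Why the interval and not the p-value.** On the same inputs, the chance that a two-sided 5% test on the intervention arm's Time 2 to Time 3 change misses a true loss is:

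| Sample, true loss | No attrition | 33% | 50% |
|---|---|---|---|
| Educators, 0.25 SD | 41–65% | 56–74% | 66–79% |
| Parents, 0.25 SD | 6–39% | 18–51% | 30–59% |
| Educators, 0.50 SD | 1–13% | 5–25% | 13–37% |
| Parents, 0.50 SD | at most 7% | at most 7% | at most 7% |

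A non-significant decline would therefore say little for educators, and less as the sample shrinks.

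**The case against.** The strongest reply is that the Time 3 sentence is a directional expectation and not a formal hypothesis. No section defines a Time 2 versus Time 3 test, makes maintenance a success criterion, or says how a non-significant change will be read. This stands. A reader might infer that the plan would let a non-significant decline pass as maintenance. The article contains no such rule, so that charge cannot be made.

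A reader might also call this an equivalence claim that lacks a margin. That does not hold either. Maintained or improved points in one direction only. A margin is a detail that a condensed article may leave to its analysis plan, and the documents offer no basis for any particular value, 0.25 SD included.

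It can further be said that the three-level model uses all three assessments and could yield the intervention arm's own changes, including whether improvement over Time 1 is still present at Time 3. That is true, and it is why the fix is cheap. But the article states its effect as a contrast between groups and names a before-and-after look for controls only.

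Finally, the miss rates rest on assumed inputs. With r = 0.8 and no attrition, the chance of missing a 0.25 SD loss falls to 24–40% for educators and 1–18% for parents. The figure of 0.5 SD is a detectable difference for parents, not a predicted gain for educators. This also stands, and the rates serve only as illustration.

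None of these replies touches the comparator. Controls have had the programme by Time 3, so the arm difference there cannot answer the durability question.

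**Conclusion.** The point holds as a mismatch between the Time 3 expectation and the between-arm effect measure that the article states. It follows from the article's own timetable and needs no numerical assumption. The Time 3 arm difference is zero when a gain is fully kept and matched, and also zero when it is fully lost and controls gain nothing.

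The point does not reach further. It does not show that the authors plan to read non-significance as maintenance, that a margin is required, or that the trial cannot describe durability at all. The Time 1 to Time 2 comparison, on which the first expectation rests, is unaffected provided that it is estimated as that contrast.

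The precision figures depend on the assumed correlation, service variance, arm sizes and attrition. They indicate that the within-arm estimate may be too imprecise for educators to separate a kept gain from a halved one, and that it is better for parents.

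**What to change.** In the analysis plan, before Time 3 data are examined (Trial status reports that follow-up data are yet to be collected):

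1. Define the randomised intervention effect as the between-arm difference in change from Time 1 to Time 2. State that the Time 3 arm difference is not evidence for or against maintenance.
2. Assess maintenance within the intervention arm. Report the Time 3 minus Time 2 change and the Time 3 minus Time 1 change, each with a 95% confidence interval that accounts for service clustering.
3. Label both as uncontrolled estimates, since time trends and selective dropout cannot be separated from the programme's lasting effect.
4. Base any statement on maintenance on the size of loss that the interval leaves open, and do not report a non-significant decline as maintenance.

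The cost is a few sentences and two contrasts from questionnaires that are already scheduled. The price is a durability conclusion that is descriptive and non-randomised and that may remain open for educators.
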